# Weighted Blankets for Agitation in Hospitalized Patients with Dementia: Protocol for a Randomized Controlled Trial

**DOI:** 10.2196/57264

**Published:** 2025-02-26

**Keywords:** dementia, hospitalized dementia patients, agitation, aggression, behaviors, sleep, weighted blankets, nonpharmacologic strategy, pilot study, inpatients, occupational therapy

## Abstract

**Background:**

There are limited therapies approved for the treatment of aggression and agitation in patients with dementia. While antipsychotics and benzodiazepines are commonly used, these medications have been associated with significant side effects and US Food and Drug Administration (FDA) boxed warnings. Weighted blankets have been associated with decreased anxiety and improved sleep. Weighted blankets are potentially a nonpharmacologic option to reduce agitation in hospitalized patients with dementia.

**Objective:**

The aim of this study is to investigate the effect of weighted blankets on aggression and agitation in hospitalized patients with dementia.

**Methods:**

A pilot study will be conducted on a total of 30 hospitalized patients with a documented clinical diagnosis of dementia and ongoing agitated behaviors admitted to a medicine or psychiatry service. Patients will be randomly allocated to receive either a weighted blanket for 3 nights or continued usual care. The primary outcome is the change in the observational version of the Cohen-Mansfield Agitation Inventory (CMAI-O) over the course of the 3-night study period. The secondary outcomes are changes in Edmonton Symptom Assessment System Revised (ESAS-r) and Clinical Global Impression (CGI) scores, hours of sleep, use of antipsychotics and benzodiazepines, and incidence of delirium. Identical study assessments will be completed for both the usual care and the weighted blanket study groups. At 5 study time points (baseline, postnight 1, postnight 2, postnight 3, and a final assessment 48-72 h after the last use of the weighted blanket), patients will be assessed with the CMAI-O, ESAS-r, and CGI tools. All assessments will be completed by the bedside nurse or patient care assistant caring for the patient each day. Within 2 to 4 weeks post discharge from the hospital, study coordinators will contact the patient’s legally authorized representative (LAR) to assess for continued use of the weighted blanket.

**Results:**

Enrollment of participants began on April 23, 2023. As of November 2024, a total of 24 participants have been enrolled in the study. Baseline characteristics of enrolled participants will be analyzed and reported upon completion of enrollment. We anticipate completing data collection by March 2026.

**Conclusions:**

The study will determine the effect of weighted blankets on agitation in hospitalized patients with dementia. Insights into the effect of weighted blankets on sleep will also be gained. The results of this study will be relevant in the setting of increasing numbers of older adults with dementia exhibiting agitation, leading to increased hospitalizations, caregiver burden, and health care costs.

**Trial Registration:**

ClinicalTrials.gov NCT03643991; http://clinicaltrials.gov/ct2/show/NCT03643991

**International Registered Report Identifier (IRRID):**

DERR1-10.2196/57264

## Introduction

### Background

Many patients with dementia develop neuropsychiatric symptoms and somewhere between 40% and 76% of patients demonstrate agitation and aggression [1,2]. Agitated behaviors are often disruptive and difficult to manage, and are associated with increased caregiver burden and burnout, increased hospitalizations, and elevated health care costs [1,3]. Agitation includes a range of behaviors, including restlessness, pacing, physical aggression, and verbal agitation [4].

Nonpharmacologic strategies are the first line in the prevention and treatment of neuropsychiatric symptoms of dementia, including agitation. Limited pharmacologic options exist in this setting. In fact, no pharmacologic therapies were approved by the Food and Drug Administration (FDA) for this indication until the recent approval of the atypical antipsychotic brexpiprazole for the treatment of agitation associated with dementia due to Alzheimer disease [5]. Other antipsychotics are commonly used, particularly in emergency and acute care settings when agitated or aggressive behaviors threaten either patient or caregiver [6]. These medications, however, are associated with significant serious long- and short-term side effects including akathisia and restlessness [7], and carry an FDA-boxed warning for increased risk of mortality [8]. The 2016 American Psychiatric Association practice guidelines recommend that antipsychotic medications be reserved for severe, dangerous, or significantly distressing symptoms and used at the lowest effective dose due to concern for side effects [9]. The management of agitated and aggressive symptoms without primary reliance on antipsychotics remains a challenge. Benzodiazepines are typically avoided due to the risk of cognitive impairment, falls, and respiratory depression [10].

Weighted blankets are filled with plastic pellets or beads and are commercially available in weights ranging from 5 to 30 pounds. Weighted blankets have been used in occupational therapy as a form of noninvasive deep-pressure stimulation, which appears to increase parasympathetic arousal and decrease anxiety [11-13]. Weighted blankets have been studied in patients with psychiatric diagnoses in both the inpatient and outpatient settings, and they appear to be associated with decreased anxiety and improved sleep [14,15]. Weighted blankets have also been associated with improved chronic pain and reduced anger scores [16,17]. Currently, however, there are no studies investigating the use of weighted blankets to address agitation in hospitalized patients with dementia.

### Objectives

The aim of this study is to investigate the effect of weighted blankets on aggression and agitation in hospitalized patients with dementia. We hypothesize that compared to controls, patients with agitation in the setting of dementia will show reduced agitation, reduced anxiety, and potentially improved sleep while hospitalized when provided with a weighted blanket.

## Methods

### Design and Randomization

To address this question, we designed a pilot study (ClinicalTrials.gov NCT03643991) with 1:1 randomization of hospitalized patients with dementia and evidence of agitated behaviors to receive either a weighted blanket for 3 nights or continued usual care.

#### Study Population and Recruitment

Patients will be recruited from a single large tertiary care hospital. Participants are eligible for inclusion if they are 60 years or older, have a documented clinical diagnosis of dementia, and are currently admitted to either a medicine or psychiatry primary service. All participants are required to have ongoing agitated behaviors at the time of enrollment as demonstrated by an elevated CMAI-O with a score of 2, 3, or 4 on at least one aggression-related item (items 1-11 or 22-24) [18]. Patients will be excluded if they have severe pain likely to be exacerbated by the use of the weighted blanket, have significant burns or wounds for which weighted blanket use could potentially be detrimental, or are admitted on a 72-hour involuntary hold. Participants can be enrolled at any point during their hospitalization. Hospitalizations will not be prolonged for the purpose of the study. To reflect real-world conditions, all other usual medical care will be continued at the discretion of the primary medical or psychiatric team.

#### Intervention

Participants will be randomized 1:1 to either the usual care group or the weighted blanket group. The weighted blankets used are commercially available and purchased for the study. Patients randomized to the weighted blanket group will be provided with either a 10 lb, 15 lb, or 20 lb weighted blanket, ensuring that the weight is not more than 10% of the participant’s body weight. Participants will be withdrawn from the study if they refuse the blanket or are unable to tolerate it for more than 2 hours on the first night after enrollment. Participants can also be withdrawn from the study at any time if the primary team feels that further participation will jeopardize patient safety. Enrolled participants will use the blanket for a total of 3 consecutive nights, or until the time of discharge if that occurs sooner. Following participation in the study, participants will be allowed to keep the weighted blanket for future personal use. To reduce potential bias, the data analysis team will remain blinded to group assignment during statistical analyses, although investigators administering the questionnaires will not be blinded due to the nature of the intervention.

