### Data Collection, Management, and Confidentiality

Participants will be randomized 1:1 to the treatment and usual care groups via computer-generated sequence which will be concealed until after each patient’s enrollment. Given the nature of the study, blinding of caregivers and study coordinators to treatment groups is not feasible.

Data will be collected by study personnel in a manner consistent with patient confidentiality. For patients withdrawn from the study, no further data will be collected but existing study data to the point of withdrawal will be included in the final analysis which will be performed based on intention to treat.

All data obtained will be entered into REDCap (Research Electronic Data Capture), a secure electronic database that is password-protected and accessible only to the study team. Each participant will be assigned a unique identification code to protect their identity, and only the code will be used for forms, reports, and data analysis. Paper records containing protected health information will be maintained in locked file cabinets in a secure room accessible only to research personnel. All patient information will be kept confidential and managed according to the Health Insurance Portability and Accountability Act of 1996 requirements.

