### Data Analysis

A per-protocol analysis will be used. Baseline characteristics of participants will be reported using percentages for categorical variables and mean with SD for continuous variables. Differences between the 2 treatment groups for the descriptive variables will be compared using chi-square tests for categorical variables and Kruskal-Wallis tests for continuous variables. The medications and dosages taken during the study will also be reported. The primary outcome of the CMAI-O score will be described at each of the 5 time points (baseline, day 1, day 2, day 3, and day 72 follow-up). A linear mixed effects model with time as a random effect will be used to analyze changes in the CMAI-O score over time. Both the unadjusted and an adjusted model with age, sex, and unit type as covariates will be reported. Age and sex were included as covariates as they are standard demographic factors that can influence behavioral outcomes. Unit type (medicine vs psychiatry) was included as it may impact patient management practices and potentially influence study outcomes. This model also allows for missing data which occurs in the dataset when a patient was discharged before the end of the study period. Secondary outcomes of ESAS-r and CGI scores will be analyzed in a comparable way with a linear mixed model. The end-of-study survey results will be described for each question. A per-protocol analysis will evaluate only the enrolled patients who followed protocol.

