## Results

Enrollment of participants began on April 23, 2023. As of November 2024, 24 participants have been enrolled in the study. Baseline characteristics of enrolled participants will be analyzed and reported upon completion of enrollment. We anticipate completing data collection by March 2026. The study results will be reported in a peer-reviewed journal upon completion.

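### No study blanket is permitted for a patient under 100 lb, yet the stated eligibility criteria set no minimum weight, so the weight rule acts after randomization and in one arm only

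*Protocol article*

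**What the plan says.** The Intervention section fixes two things for the blanket arm, the sizes and a cap. Patients receive "either a 10 lb, 15 lb, or 20 lb weighted blanket, ensuring that the weight is not more than 10% of the" patient's own body weight. The same section allows withdrawal for refusing the blanket, for not tolerating it on the first night, or when the primary team has a safety concern.

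Study Population and Recruitment lists the criteria: age, a dementia diagnosis, admitting service, a qualifying CMAI-O item score, and exclusions for pain, burns or wounds, and an involuntary hold. Some exclusions concern suitability for the blanket itself, for example "Patients will be excluded if they have severe pain likely to be exacerbated by the use of the weighted blanket". None concerns body weight.

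Data Collection, Management, and Confidentiality describes allocation by a "computer-generated sequence which will be concealed until after each" patient has been enrolled. It also says that the final analysis follows intention to treat. Data Analysis instead states: "A per-protocol analysis will evaluate only the enrolled patients who followed protocol".

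The Background notes that weighted blankets are "commercially available in weights ranging from 5 to 30 pounds", so sizes below the study's lightest exist.

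**The concern.** The list of blanket sizes and the cap together imply a minimum body weight that the eligibility criteria do not state. Following the article, staff first need the weight rule when choosing a blanket, which is after randomization and only in the blanket arm. For a patient who is too light they have three options: give no blanket, exceed the cap, or drop the patient. No withdrawal rule is written for this case, and none of the three can arise in the usual-care arm.

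What is at stake is comparability. Removing light patients from one arm selects on a baseline characteristic after randomization. Keeping them untreated in the blanket arm pulls the estimated effect toward zero. Either outcome works against the aim given under Sample Size, which is to estimate effect sizes for future studies.

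**Working it through.** The article gives no figure of its own to reproduce on this point.

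**Inputs from the article**
- Blanket weights: 10, 15 or 20 lb (Intervention).
- Cap: at most 10% of body weight (Intervention).
- Target of 30 patients, randomized 1:1, so about 15 per arm (Sample Size; Intervention).
- Enrollment to date: "As of November 2024, 24 participants have been enrolled in the study" (Results).

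**Step 1: lowest body weight for each blanket.** Minimum body weight = blanket weight / 0.10.

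| Blanket | Minimum body weight |
|---|---|
| 10 lb | 100 lb (45.4 kg) |
| 15 lb | 150 lb (68.0 kg) |
| 20 lb | 200 lb (90.7 kg) |
| 5 lb (not a study size) | 50 lb (22.7 kg) |

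At 100 lb the cap is exactly 10 lb and the lightest blanket is allowed. At 99 lb the cap is 9.9 lb, and at 90 lb it is 9.0 lb; no study blanket fits either.

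**Step 2: how many patients this could touch.** The article does not give the share p of patients under 100 lb, so I assume 3%, 5% and 10%. I also assume that the 24 already enrolled split 12/12, which leaves 30 − 24 = 6 to come, about 3 of them in the blanket arm. The expected number is n × p. The chance of at least one is 1 − (1 − p)^n.

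| Assumed p | Expected of 15 | At least one of 15 | Expected of 12 enrolled | Expected of 3 to come | At least one of 3 |
|---|---|---|---|---|---|
| 3% | 0.45 | 37% | 0.36 | 0.09 | 9% |
| 5% | 0.75 | 54% | 0.60 | 0.15 | 14% |
| 10% | 1.5 | 79% | 1.20 | 0.30 | 27% |

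One patient is 1/15, or about 7%, of the blanket arm.

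**Step 3: effect on the estimate.** Under intention to treat, suppose an untreated blanket-arm patient responds as in usual care and the blanket's effect d is the same in everyone else. The expected difference is then (1 − p) × d, a dilution of 3% to 10%. Under the per-protocol wording, such a patient would probably be excluded, although the section does not say how to class someone for whom no blanket was permitted. An equally light usual-care patient has no reason to be excluded.

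**The case against.** The strongest reply is that this is a condensed article. The full IRB-approved protocol is not shown, and a screening checklist or blanket-sizing instruction could sit there. The article does not say when weight is checked, and concealing the allocation does not prevent a weight check at screening. A team bound by the cap might treat it as an implied condition of entry. The bias argument also depends on which analysis population governs, which is a separate problem, and the refusal and intolerance rules already permit loss from one arm. Finally, the share under 100 lb is unsourced, the expected counts are small for a pilot with no powered test, and a new eligibility rule after 24 of 30 patients affects few people and makes late entrants differ from early ones.

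Much of this stands. The unseen protocol may settle the matter, the size is assumed and small, and an amendment alone protects few patients. It does not remove the inconsistency. The article prints the sizes, the cap and several blanket-suitability exclusions, and what it prints does not fit together. It frames the cap as a rule for patients already randomized to the blanket and leaves no stated route for those it rules out. That other one-sided losses exist is no reason to keep one that a baseline measurement can prevent.

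**Conclusion.** The concern holds. Under the stated rules no blanket is available below 100 lb (45.4 kg), and the stated criteria let such a patient be randomized. That threshold is exact and needs no outside figure.

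The practical size is probably small: about half a patient to one and a half patients in the whole blanket arm, most of that expectation among those already enrolled. This rests on the assumed 3% to 10% share and the assumed even split. The dilution figure also assumes no benefit without a blanket and a constant effect otherwise. If the full protocol already requires a weight check before randomization, what remains is to say so. The point is worth correcting because the remedy is cheap, not because the expected bias is large.

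**What to change.** **Preferred at this stage:** add a minimum body weight of 100 lb (45.4 kg) to the eligibility criteria, checked at screening before randomization so that it binds both arms equally. The cost is one line of text, an IRB amendment and slightly narrower eligibility.

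**Alternative:** add a 5 lb blanket, with a 50 lb (22.7 kg) minimum checked before randomization. This keeps lighter patients in, but at a lower relative dose: 5/99 is about 5% of body weight for someone just under 100 lb.

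**In either case:** check the recorded weights of everyone already enrolled, in both arms, and report the number under 100 lb by arm. If a per-protocol set leaves these patients out, apply the weight rule to usual-care patients as well. Weight is a baseline variable, so this is possible in both arms. The chart check needs no change to eligibility, and weight is already required to choose a blanket. With most patients enrolled, this step is likely to do more than the amendment.

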#### Primary Outcome

The primary end point will be the change in CMAI-O over the course of the 3-night study period. The CMAI-O is a validated scale published in 2020 by Griffith et al [18] to quantify neuropsychiatric behavior in patients with dementia. Observers rank the frequency of 29 behaviors grouped into categories: physical aggressive behaviors (questions 1-11), physical nonaggressive behaviors (questions 12-21), verbal aggressive behaviors (questions 22-24), and verbal nonaggressive behaviors (questions 25-29). The frequency of each behavior is ranked as 1 (never), 2 (less than once per h), 3 (once per h), and 4 (several times per hour).

#### Secondary Outcomes

Secondary end points will include change in Edmonton Symptom Assessment System Revised (ESAS-r) score and change in Clinical Global Impression (CGI) score as well as hours of sleep, use of antipsychotics and benzodiazepines, and incidence of delirium.

The ESAS-r was originally designed as a self-report tool in which patients rate the severity of 9 symptoms on a scale from 0 to 10 (10 being the most severe) [19]. The tool assesses the following nine symptoms: pain, tiredness, drowsiness, nausea lack of appetite, shortness of breath, depression, anxiety, and well-being. This assessment tool has been commonly used in palliative medicine and oncology settings, translated into several languages, and is well received by patients and nursing staff [19]. The ESAS-r captures the pattern of a patient’s severity of symptoms at a point in time and may be repeated to track changes over time. Since patients with a diagnosis of dementia vary significantly in their ability to report symptoms, we have standardized the protocol by using caregiver (nurse or patient care assistant) input to complete the ESAS-r assessment tool [19].

The CGI scale is a brief, independent assessment initially designed to summarize a caregiver’s view of a patient’s global functioning before and after initiating an intervention [20]. The CGI consists of 2 one-item measures that evaluate the severity of psychopathology and change from the initiation of treatment on a 7-point scale. The CGI may be used to track clinical progress over time [20].

Further clinical data will be extracted from the medical record. Caregiver staff will estimate hours of sleep. Use of antipsychotics and benzodiazepines will be recorded based on the medical administration records. The incidence of delirium will be estimated based on documentation of a newly positive Brief Confusion Assessment Model (bCAM) assessment [21]. Delirium Triage Screen and bCAM assessments are performed to screen for delirium every 12 hours (once per nursing shift) in the hospital where this study will be conducted.

#### Study Timeline and Follow-Up

Identical study assessments will be completed by the patient’s caregiver (either registered nurse or patient care assistant) for both the usual care group and the weighted blanket study group. Cohen-Mansfield Agitation Inventory (CMAI-O), ESAS-r, and CGI scores will be collected at 5 study time points (baseline, postnight 1, postnight 2, postnight 3, and a final assessment 48-72 hours after the last use of the weighted blanket). A total of 3 nights were determined to be sufficient for assessing trends in agitation, anxiety, and sleep, while also testing the feasibility of the intervention in a real-world clinical environment. Within 2-4 weeks following hospital discharge, study coordinators will contact the patient’s legally authorized representative (LAR) to assess for continued use of the blanket. Refer to the patient timeline (Table 1).

**Table 1 table1:** Patient timeline.

Assessment	Baseline (enrollment)	WB^a^ day 1	WB day 2	WB day 3	Final within 72 hours of last use of WB (cohort 1) or no WB (cohort 2)	Within 2-4 weeks post discharge
CMAI-O^b^	✓	✓	✓	✓	✓	
ESAS-r^c^	✓	✓	✓	✓	✓	
CGI^d^	✓	✓	✓	✓	✓	
Posthospitalization phone call to assess continued weighted blanket use						✓

^a^WB: weighted blanket.

^b^CMAI-O: Cohen-Mansfield Agitation Inventory.

^c^ESAS-r: Edmonton Symptom Assessment System Revised.

^d^CGI: Clinical Global Impression.

#### Sample Size

We will target an enrollment of 30 participants in this pilot study. This sample size was chosen to balance the need for gathering preliminary data with the constraints of patient availability, time, and resources within our hospital setting. The sample size of 30 is sufficient to provide preliminary insights into the effects of weighted blankets on agitation, allowing us to explore trends and estimate effect sizes for future studies. Recruitment will be facilitated by daily review of hospital-wide behavior emergency response team activations and patient referrals from inpatient medicine and psychiatry primary services.

